### **8.2. Concomitant medications and concomitant therapies**

If Grade 4 leukopenia or neutropenia is observed, G-CSF may be used within the scope of insurance coverage. However, G-CSF agents should not be administered on the same day as anticancer agents. If thrombocytopenia, nausea/vomiting, hypersensitivity, or other adverse events occur, aggressive symptomatic treatment should be given as necessary.

### 8.3. Testing and supportive care for HBs antigen-negative, HBc antibody-positive and/or HBs antibody-positive cases

The “Guideline for the prevention of hepatitis B caused by immunosuppression and chemotherapy” recommend that HBs or HBc antibodies should be measured even in HBs antigen-negative cases, and that HBV-DNA quantification should be performed in positive cases.

In HBs antigen-negative cases and HBs antibody- or HBc antibody-positive cases, it has been reported that the use of strong immunosuppressive drugs can cause reactivation of HBV, resulting in the development of severe hepatitis. Therefore, based on the “Guideline for the prevention of hepatitis B caused by immunosuppression and chemotherapy” by the Ministry of Health, Labour and Welfare Research Group “Research on refractory liver and biliary tract diseases (PI: Hirohito Tsubouchi)” and “Research on standardization of treatment for viral liver diseases including cirrhosis (PI: Hiromitsu Kumada)”, the following tests should be performed before starting chemotherapy, and the following supportive care is recommended according to the test results. It is strongly recommended that a hepatologist should be consulted when administering entecavir. However, patients positive for HBs antibody alone and have a clear history of HBV vaccination should be excluded.

#### Response to hepatitis B virus in this study

HBs antigen positive → registration prohibited

HBs antigen negative → HBc antibody and HBs antibody negative → Normal response

HBs antigen negative → HBc antibody and HBs antibody positive → Although HBV-DNA quantification is recommended, detailed measures are left to the each institution (nucleic acid analog administration, regular monitoring of hepatitis, etc.)

#### 1) Tests performed before starting chemotherapy: HBV-DNA quantification

HBV-DNA quantification is performed by PCR or real-time PCR method. The real-time PCR method with higher detection sensitivity is preferred.

#### 2) If HBV-DNA quantification is above detection sensitivity at the time before the start of chemotherapy

Give entecavir as in HBs antigen-positive cases.

##### (1) Test: HBV-DNA quantification

HBV-DNA quantification should be performed every 4 weeks from the start of chemotherapy until 12 months after the end of entecavir administration after completion of chemotherapy. However, if the patient is receiving entecavir and HBV-DNA quantification has less than detection sensitivity, the testing interval may be extended to allow for the duration of outpatient visits.

Testing for HBe antigen and HBe antibodies is also recommended as appropriate.

##### (2) Drug used: entecavir hydrate tablets (Bristol-Myers: Balaclude tablets 0.5 mg)

According to the dosage and administration listed below, entecavir should be started as soon as possible before and after the start of chemotherapy and continued for at least 12 months after the end of chemotherapy. If treatment with entecavir is to be terminated after 12 months of chemotherapy, the patient should consult a hepatologist to confirm that HBV-DNA quantification is less than detection sensitivity and to decide when to terminate treatment. Patients should be carefully monitored by HBV-DNA quantification, bearing in mind that reactivation is possible even after termination of entecavir treatment.

- Dosage and administration: Orally administered on an empty stomach (at least 2 hours after a meal and at least 2 hours before the next meal).

- Dosage:

| Creatinine clearance (mL/min) | Dose                     |
|-------------------------------|--------------------------|
| ≥ 50                          | 0.5 mg once daily        |
| ≥ 30 and < 50                 | 0.5 mg once every 2 days |

|               |                          |
|---------------|--------------------------|
| ≥ 10 and < 30 | 0.5 mg once every 3 days |
| < 10          | 0.5 mg once every 7 days |

3) HBV-DNA quantification with less than detection sensitivity at the time before chemotherapy  
Monitoring by either HBV-DNA quantification or liver function (AST, ALT).

(1) Tests: HBV-DNA quantification or liver function (AST, ALT)

The MHLW Research Group guidelines recommend monitoring by HBV-DNA quantification every 4 weeks during chemotherapy and for 12 months after chemotherapy. However, the guideline was developed based on data from high-risk cases of HBV reactivation, such as chemotherapy with rituximab, and there is limited evidence for solid tumors, so there is room for consideration of cost-effectiveness in chemotherapy cases where the risk of reactivation is expected to be low. Other than periodic HBV-DNA quantification monitoring, a countermeasure method that involves careful liver function (AST, ALT) monitoring and HBV-DNA quantification as appropriate if abnormalities are observed is an option. However, careful monitoring is necessary because there have been reports of failure to save lives (death due to fulminant hepatitis) when antiviral drugs were administered after hepatotoxicity and hepatitis due to HBV reactivation had occurred.

In view of the above background and the risk of HBV reactivation by chemotherapy, monitoring by either HBV-DNA quantification or liver function (AST, ALT) is strongly recommended in this study. If HBV-DNA quantification is above the detection sensitivity, entecavir should be started immediately according to the dosage and administration described in 2) above.

## **9. Anticipated adverse drug events**

### **9.1. Drug information**

Generic name: S-1, Trade name: TS-1, Manufactured and distributed by Taiho Pharmaceutical Co. For details, please refer to the product document. The latest information can be found at <http://www.info.pmda.go.jp/>.

### **9.2. Definition of adverse events**

An adverse event is any unwanted or unintended sign (including abnormal changes in laboratory values), symptom, or illness that occurs in a subject as a result of receiving the study treatment, whether or not causally related to the study treatment.

### **9.3. Assessment of adverse events/adverse reactions**

The NCI Common Terminology Criteria for Adverse Events v4.0 (Japanese translation; attached) will be followed. An adverse event is defined as a Grade 1 or greater deterioration from the baseline level.

### **9.4. Anticipated adverse reactions**

Refer to the respective attachment. For the latest information, check <http://www.info.pmda.go.jp/>.

### **9.5. Causal relationship with study drug**

In determining the causal relationship of an adverse event to the study drug, the subject's general condition, complications, concomitant medications/adjunctive therapies, and temporal relationship should be taken into consideration. The causal relationship will be judged by using two categories: "there is a reasonable causal relationship with the study drug" and "there is no reasonable causal relationship with the study drug". Among adverse events, those with a reasonable causal relationship to the study treatment shall be treated as adverse reactions.

## **10. Reporting adverse event**

In the event of a "serious adverse event" or "unanticipated adverse event", the principal investigator in each

institution will report it to the principal investigator/research secretariat.

The responsibility for reporting to the head at each institution, spontaneous reporting from medical institutions to the Pharmaceutical Affairs Bureau of the Ministry of Health, Labour and Welfare under the “Safety Information Reporting System for Drugs and Other Drugs”, a Ministry of Health, Labour and Welfare project, and spontaneous reporting from medical institutions to companies under the “Company Reporting System” under the Pharmaceutical Affairs Law shall be handled appropriately by the principal investigator at each institution in accordance with the regulations of each institution. The responsibility of the principal investigator of each institution shall be to make appropriate reports in accordance with the regulations of each institution.

#### 10.1 Adverse events requiring urgent reporting

Adverse events that fall into any of the following categories are subject to urgent reporting.

- (1) All deaths during protocol treatment or within 30 days of the last protocol treatment date.

The presence or absence of a causal relationship with the protocol treatment is not required. In the case of discontinued protocol treatment, even if post-treatment has already started, the case is eligible for urgent report if it is within 30 days of the last protocol treatment date (“30 days” refers to 30 days counting from the day after the last protocol treatment date, which is day 0).

- (2) Unexpected Grade 4 non-hematologic toxicity (adverse events outside the blood/bone marrow category in CTCAEv.4.0-JCOG): those not described in the most recent product document.

#### 10.2. Adverse events requiring normal reporting

Adverse events that fall into one of the following categories are subject to normal reporting

- (1) Deaths after 31 days from the last protocol treatment date for which a causal relationship to protocol treatment cannot be ruled out. Deaths suspected to be treatment-related deaths fall under this category. Obvious deaths of the disease are not applicable.
- (2) Anticipated Grade 4 non-hematologic toxicity (adverse events outside the blood/bone marrow category in CTCAEv.4.0-JCOG)
- (3) Unexpected Grade 3 adverse events  
Grade 3 equivalent adverse events that do not fall under the “Expected adverse drug events” section.
- (4) Permanent or significant impairment  
Aplastic anemia, myelodysplastic syndrome, secondary cancers, etc.
- (5) Other serious medical events  
Information that does not fall into any of the above categories, but is deemed important information that should be shared by the principal investigator and all institutions in the research group

#### 10.3. Reporting obligations and procedures of the institutional principal investigators

##### Urgent report

- (1) Primary report: The physician in charge of the case should fill out the “AE/AR/ADR Rapid Primary Report” within 72 hours, fax/telephone the form to the research secretariat, and also report to the institutional principal investigator as soon as possible.
- (2) Secondary report: Prepare an “ADR Report Form” and a “Detailed Case Report (A4 free-form)” with details, and fax both to the research secretariat within 7 days.
- (3) Tertiary report: In principle, complete all the prescribed items on the “ADR Report Form” and fax a copy to the research secretariat within 15 days of learning of the occurrence of the adverse event.
- (4) Additional report: If there is additional information obtained after the tertiary report, such as an autopsy report in the case of death, or if there is additional information that was not completed in the tertiary report, it should be reported to the research secretariat.

##### Regular Report

- (1) Report within 15 days according to the “ADR Report” and in accordance with the urgent report.

#### 10.4. Responsibilities of principal investigator/research secretariat

- (1) Determining whether there is a need to suspend registration and emergency notification to the institutions

Upon receiving a report from the principal investigator, the principal investigator or secretariat will determine the urgency, importance, and degree of impact of the report and, if necessary, take measures such as suspending the registration (contacting the registration center and all participating institutions) or urgently notifying the participating institutions of the matter. Depending on the level of urgency, the registration centers and institutions may be contacted by telephone, but will also be notified in writing (fax, mail, e-mail) as soon as possible afterwards.

- (2) Report to the Data and Safety Monitoring Committee

If the principal investigator/research secretariat determines that an adverse event reported by an institution as an urgent or routine report constitutes a “reportable adverse event”, it should be reported in writing (fax, mail, or e-mail) to the Data and Safety Monitoring Committee within 15 days of learning of the occurrence of the adverse event, and at the same time, the principal investigator/research secretariat should request a review of the principal investigator’s opinion regarding the adverse event and the adequacy of the response to the adverse event. At the same time, the Committee will request a review of the opinion of the principal investigator regarding the adverse event and the appropriateness of the response to the adverse event.

### 11. Observation/test items and timing

#### 11.1. Definition of treatment period

The treatment period for each subject is from the date of enrollment until 4 weeks after the last dose or until the start of post-treatment within 4 weeks of the last dose.

The principal investigator or a research associate investigator will investigate and confirm the following information prior to enrollment and initiation of administration

#### 11.2. Preoperative endpoints

Chest X-ray/CT, head CT or MRI, abdominal CT, bone scintigraphy. PET can be substituted for abdominal and bone lesion search.

#### 11.3. Pre-treatment (at enrollment) endpoints (within 2 weeks prior to enrollment)

- 1) Patient background

Sex, age, height, weight, body surface area, date of surgery, pathological stage (stage and TNM classification), medical history, PS, histopathology findings, complications and disease name and treatment, concomitant medications, smoking history (number multiplied by duration)

- (2) Subjective and objective symptoms

Gastrointestinal symptoms such as nausea/vomiting, fatigue, fever, skin symptoms, dysgeusia, dyspnea, and other symptoms

- (3) General blood/biochemistry/gas

General blood (leukocytes/fraction, hemoglobin, platelets)

Blood biochemistry (Alb, T-Bil, AST, ALT, LDH, BUN, Ccr or Cr, Na, K, Cl, Ca, CRP)

Blood gas test or SpO2

- 4) Observation of targeted lesions: chest X-ray, chest CT if necessary

- 5) Tumor markers: CYFRA, CEA

- 6) Urinalysis: protein, sugar, urobilinogen, occult blood

#### 11.4. Endpoints during treatment period

Evaluate various test items and the subject’s condition.

- |                                       |                        |
|---------------------------------------|------------------------|
| 1) General condition:                 | PS, weight measurement |
| 2) Subjective and objective symptoms: | Same as 11.3 (2)       |
| 3) General blood/biochemistry/gas:    | Same as 11.3.(3)       |

- 4) Observation of targeted lesions: Same as 11.3.(4)  
 5) Tumor markers: Same as 11.3.(5)  
 6) Urinalysis: Same as 11.3.(6)

| Item/Period                                           | Before the start of treatment | During treatment (every 1–2 weeks)                | At the end of treatment |
|-------------------------------------------------------|-------------------------------|---------------------------------------------------|-------------------------|
| Patient background                                    | ○                             |                                                   |                         |
| Subjective and objective findings and PS              | ○                             | ○                                                 | ○                       |
| Target lesion observation (Search for new lesions)    | ○                             | In principle, every 2 months (Enforced as needed) | ○                       |
| General blood/biochemistry/gas and weight measurement | ○                             | ○                                                 | ○                       |
| Tumor marker                                          | ○                             | In principle, every 1 month*                      | ○                       |
| Urinalysis                                            | ○                             | as necessary                                      | as necessary            |

If any adverse events occur, they should be treated as often as possible to allow adequate observation of their progress (e.g., most abnormal, date of recovery or lightening), even if they occur on days other than those specified in all the above items.

\*This will be performed within the scope of insurance coverage.

#### 11.5. After discontinuation/termination of drug administration

After discontinuation/termination of treatment to a total of 2 years after the first administration

As a rule, an examination and chest X-ray should be performed every 3 months. Imaging tests including chest CT, tumor markers (CEA, CYFRA) every 3 to 6 months, and blood tests (hemoglobin, white blood cell count and fraction, platelet count, Alb, T-Bil, AST, ALT, LDH, BUN, Cr, Na, K, Cl, Ca) as necessary.

After discontinuation/termination of treatment to a total of 3 to 5 years after the first administration

As a rule, an examination and chest X-ray should be performed every 6 months. Imaging tests including chest CT, tumor markers (CEA, CYFRA) every 6 to 12 months, and blood tests (hemoglobin, white blood cell count and fraction, platelet count, Alb, T-Bil, AST, ALT, LDH, BUN, Cr, Na, K, Cl, Ca) as necessary.

#### 11.6. With signs of recurrence

At any time after surgery, any sign of recurrence should be investigated (chest CT, bone scintigraphy, head CT or MRI, abdominal CT, PET scan if necessary, etc.).

## 12. Evaluation methods of assessment items

### 12.1. Evaluation items

Primary endpoint : Treatment completion rate (Feasibility)

Secondary endpoints: rate and severity of adverse events, recurrence-free survival (RFS), overall survival (OS)

### 12.2. Evaluation method

Treatment completion rate (Feasibility)

Definition of treatment completion

Patients who have completed six months of treatment with S-1 as postoperative chemotherapy with a dose reduction/withdrawal ratio of at least 70% while following the dose reduction/withdrawal criteria specified in the protocol are defined as those who have completed the protocol treatment (completed administration).

S-1 actual total dose/planned total dose ratio

Percentage of doses administered (%) = Total actual prescriptions during the entire dosing period (mg)/total scheduled doses (mg) x 100

However, total expected dose = initial dose (mg/day) x total expected days (days), and

Defined as the sum of the actual doses taken during the entire treatment period (mg) =  $\Sigma$  (total doses taken up to 6 months or until treatment discontinuation), where  $\Sigma$  (total doses taken up to 6 months or until treatment discontinuation).

Finally, for the primary endpoint, the proportion of patients who “completed the protocol” to all eligible patients will be calculated, excluding those who discontinued or dropped out of the protocol due to recurrence. The completion rate at 9 months, 1 year, etc. of protocol treatment will also be calculated.

Recurrence-free survival (RFS)

The period beginning on the date of registration and ending on the earlier date on which the patient is determined to have relapsed or the date of death from any cause.

The term “recurrence” includes both diagnostic imaging and clinical relapse, which is defined as an exacerbation of a disease condition that is not diagnosed by imaging. In the case of a recurrence determined based on imaging diagnosis, the date of recurrence is the date of the examination that performed the imaging test. A period of elevated tumor markers alone shall not be considered as recurrence, but the date of examination when recurrence is confirmed by diagnostic imaging or the date of clinical judgment of recurrence due to worsening of the disease condition shall be considered as recurrence.

In the case of a surviving patient who has not been judged to have relapsed, the last date of confirmation of survival shall be the date of termination. (Survival confirmation by phone call is also acceptable, but the fact that survival confirmation was made must be recorded in the medical record.)

In cases where chemotherapy is discontinued due to toxicity or patient refusal, and other treatments are added as post-treatment, the event and discontinuation are treated in the same manner. In other words, the discontinuation is not considered at the time of treatment discontinuation or at the date of start of post-treatment.

When the diagnosis of recurrence is based on diagnostic imaging, the event is defined as the “date of examination” of the imaging test on which a “confirmed diagnosis” is obtained at a later date, not the date of examination of the “suspected diagnosis on imaging”. If the recurrence is clinically determined to be a recurrence without imaging diagnosis, the event shall be defined as the date when the recurrence is determined to be a recurrence.

When the definitive diagnosis of recurrence is made by biopsy pathology, the event shall be the date of clinical diagnosis if the recurrence can be diagnosed clinically before biopsy, or the date of biopsy if the recurrence cannot be diagnosed clinically but is diagnosed by biopsy pathology.

The occurrence of a second cancer (iatrogenic overlapping cancer) is neither an event nor a censored event, but rather a recurrence-free survival period until another event is observed.

削除: Relapse

削除: relapse

Differences in recurrence-free survival stratified by completion rate will also be identified.

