## **7. Protocol treatment discontinuation, termination criteria, and subsequent therapy**

### **7.1. Criteria for discontinuation of protocol treatment**

If any of the following criteria are met, the physician in charge will discontinue protocol treatment

- 1) If protocol treatment cannot be started 28 days after the last day of S-1 treatment (which corresponds to 21 days after the scheduled start of the next course in Arm B) (in this case, the day after the last day of S-1 treatment is considered Day 1). Starting administration on the same day of the week is acceptable).
- 2) If a withdrawal of more than 28 days is required (in this case, the day after the last day of S-1 administration shall be considered as Day 1. Resumption on the same day of the week 4 weeks after the date of the last dose is acceptable)
- 3) When an adverse event that meets each of the dose reduction criteria occurs even if the S-1 dose is reduced to the lowest level  
Or if a Grade 4 non-hematologic toxicity (Grade 1 or higher for pulmonary inflammation) develops.
- 4) When an adverse event occurs that makes it difficult to continue administration
- 5) If the physician in charge determines that the disease has recurred
- 6) If the patient requests discontinuation
- 7) When matters that should be excluded from the subjects turned out after registration
- 8) Other cases in which the physician in charge deems it necessary to discontinue the study.

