#### Overall survival (OS)

The period beginning on the date of the first postoperative administration of S-1 and ending on the date of death from any cause.

In surviving cases, the last date of confirmation of survival is the date of termination (telephone confirmation of survival is also acceptable, but should be documented in the patient's medical record). (Survival confirmation by phone call is also acceptable, but the fact that the patient survived must be recorded in the patient's medical record.)

In the case of untraceable cases, the last date of confirmed survival prior to the loss of follow-up is considered to be the termination date.

Differences in survival stratified by percentage of completion will also be identified.

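### Comparing RFS and OS by treatment completion, with the clock starting before completion can be known, makes completers look better even if completion has no effect

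*Protocol*

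**What the plan says.** All of this is in the protocol.

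- **RFS clock (Section 12.2):** "The period beginning on the date of registration and ending on the earlier date on which the patient is determined to have relapsed", or has died from any cause if that is earlier.
- **OS clock (Section 12.2, Overall survival):** "The period beginning on the date of the first postoperative administration of S-1 and ending on the date of death from any cause".
- **Completion (Section 12.2):** "Patients who have completed six months of treatment with S-1 as postoperative chemotherapy", with a ratio of at least 70%. The section adds: "The completion rate at 9 months, 1 year, etc. of protocol treatment will also be calculated".
- **Recurrence ends treatment (Section 7.1, item 5):** "If the physician in charge determines that the disease has recurred".
- **Comparisons by completion (Section 12.2):** for RFS, "Differences in recurrence-free survival stratified by completion rate will also be identified". For OS, "Differences in survival stratified by percentage of completion will also be identified".

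Neither sentence mentions a landmark, a time-dependent covariate or a descriptive label. The calculation of the primary completion rate is made "excluding those who discontinued or dropped out of the protocol due to recurrence". That exclusion is stated for the primary endpoint and is not repeated for RFS or OS.

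**The concern.** Patients are grouped by something that happens after the clock has started. To be a completer, a patient must first live six months on treatment without a recognised recurrence. That time is credited to completers as event-free follow-up, although they could not have had an event in it and stayed completers. Early RFS events all go to the other group. Completion at 9 months or 1 year lengthens the protected period.

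For OS, early deaths are sorted in the same way. In addition, a patient who recurs early but survives past six months becomes a non-completer and brings a poor prognosis into that group.

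At stake is the interpretation of the two announced comparisons. A reader could take the difference as evidence that finishing S-1 prolongs survival, when it would arise with no effect at all.

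**Working it through.** **The plan's own figures.** The protocol gives no figure for these comparisons. The completion rates borrowed below (55% and 40%) come from the selection design in Section 13.3, which reproduces. The normal approximation gives 35.6 (unpooled variance) or 36.4 (pooled), so 36 to 37 per group. The exact probability of correct selection at 37 per group is 90.2% with ties split.

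**Inputs.**
- 1-year event-free rate *s*: 83.7%, the 1-year DFS of the adjuvant S-1 phase II study cited in Section 2.2 (stages IB to IIIA). Range: 95% (that study's stage I figure) to 75% (its stage III figure).
- Share able to tolerate six months of treatment, *c*: 47.5%, midway between 55% and 40%.
- Assumptions: exponential RFS, and tolerance independent of prognosis, so the true hazard ratio is 1. The small gap between registration and first dose is ignored.

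**Closed form.** A completer tolerates treatment and is event-free at six months.
- Event by six months: 1 − √*s*.
- Two-year RFS, completers: *s*² / √*s* = *s*^1.5.
- Two-year RFS, non-completers: (1 − *c*)·*s*² / (1 − *c*·√*s*).

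At *s* = 0.837, √*s* = 0.915:
- Events by six months: 1 − 0.915 = 8.5%, all among non-completers.
- Completers: 0.837^1.5 = 76.6%.
- Non-completers: 0.525 × 0.7006 / (1 − 0.475 × 0.915) = 0.3678 / 0.5654 = 65.0%.

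| 1-year event-free rate | Event by 6 months | 2-year RFS, completers | 2-year RFS, non-completers | Gap (points) |
|---|---|---|---|---|
| 95% | 2.5% | 92.6% | 88.2% | 4.4 |
| 83.7% | 8.5% | 76.6% | 65.0% | 11.6 |
| 75% | 13.4% | 65.0% | 50.2% | 14.8 |

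The whole gap is artefact, since completion has no effect in this model.

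**Simulated trials of 100 patients, true hazard ratio 1.** False benefit means a log-rank result favouring completers beyond 1.96 standard errors, nominally 2.5%.
- *s* = 83.7%, follow-up 5 to 9 years, *c* from 40% to 55%: apparent hazard ratio about 0.77 to 0.82, false benefit 11% to 19%.
- Same follow-up at *s* = 95%: false benefit about 5% to 7%. At *s* = 75%: about 18% to 31%.
- *s* = 83.7%, *c* = 50%, all follow-up cut at two years: hazard ratio 0.57, false benefit 31%. This is an outer bound for the two-year analysis in Section 13.1, because early enrollees will have been followed longer.
- Patients with an event while still on treatment dropped, *s* from 75% to 95%: hazard ratio 0.90 to 0.95 at five years and 0.82 to 0.84 at two years. The bias shrinks but does not vanish, because non-completers who stopped early can still have events before six months and completers cannot.
- Six-month landmark, *c* = 50%, *s* from 75% to 95%: hazard ratio 1.00 to 1.01, false benefit 2.1% to 2.8%.

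**OS.** The documents give no overall survival rate for this population, so no figure is offered.

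**The case against.** **The protocol does not fix the method.** The two sentences name no model, test or risk set, and a landmark is often specified in a separate analysis plan, which is not at hand. That would answer a complaint about missing detail. Here the protocol states both the time origins and the grouping, and the two together produce the bias. A landmark added elsewhere would change the stated analysis.

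**Recurrence drop-outs may not count as non-completers.** Sections 12.2 and 13.3 remove them from the primary completion rate. If the same rule were carried over, the bias would be well under half as large. This stands as a limit on size. The text confines the exclusion to the primary endpoint, however, and some bias remains even with it.

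**The wording is loose.** Completion rate and percentage of completion could mean bands of dose ratio. Doses are summed to six months or to discontinuation, so an early event would still lower the ratio. If arms were compared within completion strata, the comparison would condition on a post-randomisation variable.

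**The consequence is limited.** A reader might infer that the artefact would steer the phase III choice by making completion look like a surrogate for survival. The protocol does not support that. Section 13.4 decides on arm-level completion rates and, if these are close, on arm-level toxicity, quality of life, convenience, cost, later retention, RFS and survival. RFS or OS by completion status is not a criterion, and the section itself cautions that better continuity need not mean survival benefit.

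**Conclusion.** The point holds for the two supplementary comparisons and goes no further. Followed as written, they favour completers when completion does nothing. For RFS the artefact is about 4 to 15 percentage points at two years over 1-year event-free rates of 95% to 75%. At 83.7% with five to nine years' follow-up, the apparent hazard ratio is about 0.77 to 0.82, and false benefit occurs in 11% to 19% of trials against 2.5% nominal. If patients with on-treatment recurrence are dropped, the hazard ratio is about 0.90 to 0.95 at five years.

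The direction follows from the definitions. The size rests on exponential RFS, tolerance unrelated to prognosis, and event rates from a cited study whose population differs: this trial also admits stage IA (T1bN0M0) and requires age 75 or older. No single figure should be read as the expected bias, and none is available for OS. The primary endpoint, the between-arm RFS and OS comparisons and the Section 13.4 decision rule are not affected.

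**What to change.** Replace both sentences in Section 12.2 along these lines:

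- **Landmark.** Compare RFS and OS by six-month completion only from a landmark six months after the first S-1 dose, with time counted from the landmark. Six months from registration is too early: Section 6.1 has treatment start after enrolment, as a rule within a week, so completion would not yet be known.
- **Risk sets.** For RFS, include patients alive and recurrence-free at the landmark. For OS, either use the same restriction, or report all patients alive alongside the recurrence-free subset, because early recurrence still moves poor-prognosis patients into the non-completers.
- **Later measures.** Use a 9- or 12-month landmark for completion at 9 months or 1 year.
- **Alternative.** Fit completion as a time-dependent covariate that switches on when completion is reached.
- **Label.** Call the result exploratory and non-causal. A landmark removes the guaranteed event-free time, but not the difference in fitness between those who can and cannot finish.

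The cost is about one sentence per endpoint and no new data. Patients with events before the six-month landmark leave the comparison (about 3% to 13% for RFS across these event rates). So do registered patients who never start S-1, since they have no first-dose date. The between-arm analyses keep their present definitions.
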